#### Focus group discussion (FGD)

The FGDs will be conducted at baseline to collect data on the factors that influence the demand (use and or request) for MRDT in the communities. Nine focus group discussions (FGDs) will be carried out across the three study sites/strata. Participants will be purposively selected from among providers, male and female community members (who have resided in the community for at least 2 years). There will be three focus group discussions (FGDs) with providers, one per stratum; three FGDs with male community members, one per stratum and three FGDs with female community members, one per stratum.

Investigators will administer the FGDs using a FGD question guide prepared in English and pre-tested in non-participating clusters. The FGD question guide will consist of both very open-ended and more targeted questions designed to explore the providers’ and community members’ knowledge and practice of MRDT and their perceptions of the determinants of the demand for MRDT in their communities/villages. The more targeted focus group questions are based on the proximal determinants in the study’s logical framework. The more targeted questions are combined with the very open-ended questions to identify additional determinants. Before commencement of each FGD, the investigators will collect background data on participants such as age, sex, level of education, occupation and number of years of experience in using MRDT (for providers). Each FGD will consist of 8–10 participants and will last for about 1 hour. The FGD will be audio-recorded and later transcribed (and translated) verbatim into English before analysis.

#### Provider survey

Provider survey will be conducted at baseline and end of study (3 months after the end of the intervention) to collect data for the assessment of the effect of the interventions on the knowledge and opinions of healthcare providers and their practice of health communication about malaria and malaria diagnosis. The provider survey questionnaire is similar to the household questionnaire and is modified to collect data about the following items from the healthcare providers:
Basic socio-demographic characteristicsKnowledge and opinions about malaria and malaria diagnosisThe practice of health communication about malaria and malaria diagnosisThe determinants of the demand for MRDT

#### Review of the patient register and personal medical records

Patient registers are routinely kept by public primary health facilities. The following relevant data are contained in the registers: the patient’s biodata (name, age, sex, address, etc.), date, symptoms, type of test performed, test result and type of drug given. The participating PMVs will be asked to keep similar records. The registers will be used by the research team for monitoring, supportive supervision and evaluation. The investigators will review the patient registers for 9 months pre-intervention and 9 months post end-of-intervention records. The document review will provide data for evaluating the effect of the interventions on the number of patients with suspected malaria visiting the public primary health centres.

#### Documentations of the implementation/intervention process

The process of implementation of the study will be documented including challenges encountered and how these were addressed. The social group and provider intervention processes will be documented and/or recorded with respect to the name of the participant, the participant’s phone number/contact, individual contributions, the participant’s observations and evaluation of the intervention logistics and suggestions, etc. The study personnel and the organizers of the interventions will also record their experience on challenges and possible solutions. These data will be used for monitoring and to guide the implementation of similar interventions in the future.

#### Costing of the intervention process

Direct and indirect costs of the intervention process will be assessed from the perspective of the implementer of the intervention and that of the recipient of the intervention (the societal perspective) using standard economic evaluation methods. Costs will be estimated primarily from the documentation of the implementation/intervention process and the project financial accounts. The costing will be guided by the research budget.

#### Data management plan and quality assurance

During the household surveys, the research supervisors will revisit an average of 30 households in each participating cluster with a specially designed questionnaire to double check on responses and coverage. The supervisors will collect completed questionnaires from the interviewers weekly and crosscheck/review for internal consistency and completeness. Questionnaires with internal inconsistencies and/or missing data will be returned to the respective field staff for correction with the respective respondent. The questionnaires will be serially (and uniquely) numbered and data will be double-entered using Microsoft Excel 2007 (Microsoft Inc., Redmond, WA, USA) and will be verified using Stata version 15 (Stata Corp, College Station, TX, USA). The dataset-compare utility in Stata will be used to verify the datasets and any discrepancies identified will be crosschecked against the corresponding original questionnaire and corrected before analysis. The variables and data in the dataset will also be examined in detail and range checks will be done to ensure the data were entered correctly and appropriately.

The audio recordings of the FGDs will be transcribed (verbatim) within 24 hours of recording and translated into English before analysis. The questionnaires, the audio recordings and the verbatim transcript of the FGDs will be stored in a secure area while the electronic data file will have a back-up file. Access to study materials and data files by unauthorized persons will be prevented.

#### Sample size

After comparing the required sample size for each of the primary objectives, the largest sample size will be used. This is based on the primary objective to evaluate the effectiveness of the social group/provider intervention compared to the social group intervention in increasing the demand for MRDT in the communities. The sample size is estimated using the methods recommended for a stratified, cluster-randomized trial [39, 40] and will be based on the primary outcome of the proportion of children under 5 years of age with fever or malaria-like illness, in the 2 weeks preceding a population-based household survey, who received MRDT. A plausible estimate of the primary outcome of 11% in the control arm will be used, based on the reported value for the south-east zone (that includes Ebonyi state) in the NMIS 2015 [15].

Assuming a coefficient of variation between clusters within strata of 0.16, a sample size per cluster of 40 eligible children under 5 years of age and 80% power at 5% probability of type I error, the trial will require 6 clusters per arm to detect a difference of 20% in the primary outcome between the control arm and the social group arm (an increase from 11% to 31%) and a difference of 20% between the social group arm and the social group/provider arm (an increase from 31% to 51%). A sample size per cluster (cluster size) of 40 subjects with 6 clusters per arm gives a total cluster number of 18, with 240 subjects per arm and a total sample size of 720 subjects. The sample size per cluster (of 40) will be increased by 20% (to 50) to compensate for any probable invalid records and other field eventualities. This gives a final cluster size of 50 subjects with 300 subjects per arm and a total sample size of 900 subjects.

The same sample size will be used to assess the co-primary outcome of the proportion of children ages 5 years and above and adults (excluding pregnant women) with fever or malaria-like illness, in the 2 weeks preceding a population-based household survey, who received MRDT. An equal number of clusters (*n* = 6) will be allocated to each arm and to each stratum and, despite variations in population size in the clusters, an equal fixed sample size (*n* = 50 for each target population) per cluster will be used to optimize statistical efficiency [39, 40].

Sample size is estimated for the provider survey to give the expected level of precision (at a 95% confidence level) for determining the proportion of providers that have good knowledge and opinion about malaria and malaria diagnosis. Based on the number of clusters (*n* = 6) allocated to each arm and about 7–8 individual providers per cluster who consented to participate in the study, we expect to survey 42 providers per arm (7 per cluster). Assuming the outcome measure of 50% in each of the control and social group arms and 70% in the social group/provider arm, with an intra-cluster correlation coefficient (ICC) of 0.01, we can estimate the true outcome measure with ± 15.6% precision in each of the control and social group arms and ± 14.3% precision in the social group/provider arm.

#### Sampling technique (recruitment)

Stratified multistage (cluster) sampling will be employed. We will randomly select 18 clusters from a list of eligible clusters across 3 strata (6 in each stratum) using the “sample” command in Stata. To enhance reproducibility, random-number seed will be set using the “set seed” command before running the “sample” command. If written consent is not provided by any of the selected cluster(s) before randomization, replacement cluster(s) will be randomly selected from the remaining list of eligible clusters using the same technique. The summary of the trial profile is shown in Fig. 3.

**Fig. 3 Fig3:**
[figure not shown]
Summary of the trial profile

Within the selected clusters, an average of four eligible social groups per cluster will be purposively selected and non-consenting social group(s) prior to randomization will be replaced. All eligible and consenting health facilities and the individual providers involved in the diagnosis and treatment of suspected cases of malaria will be selected across clusters before randomization. A number of eligible individual providers and community members who have resided in the community for at least 2 years will be purposively selected for the focus group discussion. All the households in the selected clusters will be enumerated and screened for inclusion during the pre-intervention and post-intervention surveys. If the required sample size is not reached after the interviewers have reached the end of the enumerated households, non-eligible households will be revisited and re-assessed to see whether they have become eligible.

#### Randomization

Randomization will be done using Stata version 12 (Stata Corp, College Station, TX, USA). A statistician that will not otherwise take part in the study will use stratified randomization to assign the 18 clusters across the 3 strata to the 3 treatment arms after written consent is obtained from all recruited participants. The six clusters within each stratum will be randomly allocated to the three study arms in the ratio of 2:2:2 using a programme written in Stata. A restricted randomization technique will be employed for the within-strata allocation, to ensure the desired balance in cluster number in the study arms. The summary of the trial profile is shown in Fig. 3.

It will not be possible to blind the interviewers who administer questionnaires in the household survey or the respondent female heads of households, because of the pragmatic nature of the trial, as they could acquire treatment knowledge from informal sources or *on the grapevine*. Some of the respondents could also be social group members or providers. It will also not be possible to blind the investigators who administer the intervention or the participants receiving the intervention (social groups and providers).

#### Data analysis

Data will be double-entered using Microsoft Excel 2007 (Microsoft Inc., Redmond, WA, USA) and analysed using Stata version 15 (Stata Corp, College Station, TX, USA). Since the number of subjects/household members on whom data will be collected is expected to vary across clusters (due to the method employed for the household survey), the “sample” command will be used to randomly select an equal number of subjects across clusters for analysis. All analyses will be on an intention-to-treat basis.

The effect of the interventions on the primary outcome will be analysed using cluster-level methods for stratified, cluster-randomized trials with a small number of clusters per treatment arm [39, 40]. Point estimates of the intervention effects (risk difference) in each intervention arm compared to control and in both of the intervention arms compared to each other will be computed from the unweighted mean of cluster-level summaries (proportions) of the outcome measures in each study arm. But since the cluster size (sample size across clusters) is constant, this point estimate will be identical to that obtained from the weighted average of individual values [39, 40]. Also, since the number of clusters across strata is constant, the estimated risk difference will be identical to the weighted average of stratum-specific risk difference.

An overall test of the null hypothesis of no difference between any of the study arms will be conducted in a two-way analysis of variance (ANOVA) of the cluster-level proportion on stratum and treatment arm. This overall test is to guide the interpretation of any subsequent significant findings in pair-wise comparisons. If the distribution of the cluster summaries in each study arm is markedly skewed, logarithmic transformation may be considered before analysis. Before conducting pair-wise significance testing and computing a confidence interval, an estimate of the within-stratum between-cluster variance will be obtained as the residual mean square from two-way ANOVA of the cluster-level proportions on stratum and treatment arm, including interaction terms. The within-stratum between-cluster variance will then be used in a stratified *t* test to test the null hypotheses of no difference in the primary outcome between each intervention arm and the control and between the two intervention arms. It will also be used in computing the corresponding 95% confidence interval of each risk difference.

Adjusted analysis based on cluster summaries will be done in a two-staged procedure. In the first stage, the covariate-adjusted residual will be obtained for each cluster using standard multiple linear regression analysis, incorporating the stratum (as a fixed effect) and all baseline cluster-level covariates of interest but excluding the intervention effect. The potential baseline covariates of interest will include cluster-level summaries of the primary outcome measure, mean scores for respondents’ knowledge and opinions (about malaria and malaria diagnosis) and other baseline variables found to differ between the study arms and which can be determinants of a particular outcome. Only cluster-level summaries of baseline covariates will be used in the adjusted analysis because baseline and follow-up data will be on different individuals, as the study employed a repeated cross-sectional design [39, 40]. The difference-residual for each cluster will be obtained as the difference between the observed outcome in each cluster and the predicted outcome in the absence of an intervention effect. The covariate-adjusted residuals will replace the cluster-level proportions in the second stage in estimating the intervention effects, which are thus adjusted for the covariates in the first stage.

The same cluster-level methods will be used to evaluate the effect of the interventions on the secondary outcomes. Comparative analysis of baseline data will be used to assess the balance between the treatment arms and potential baseline variables that will be reported include the cluster-level and individual-level summaries of the primary and secondary outcome measures, the age and sex of individual subjects, the age of the respondent female head of household, educational level, occupation, level of knowledge and opinions about malaria and malaria diagnosis and average knowledge and opinion score. Summary statistics of baseline data will be used to assess the level of demand for MRDT, care-seeking practices and pattern of anti-malarial drug use among community members with fever or malaria-like illness; the level of knowledge and opinions of the female heads of households about malaria and malaria diagnosis and the level of knowledge and opinions of healthcare providers about malaria and malaria diagnosis.

To ascertain the factors that influence the demand for MRDT in the communities, a thematic analysis of the FGDs will be performed using the method recommended by Braun and Clarke [44]. The audio recordings of the FGDs will be transcribed (and translated) verbatim into English and the transcript will be compared with the original recording to check for “accuracy” before conducting the analysis. Exact and meaning-based translation will be used. QDA Miner Lite 2 (by Provalis Research) will be used to manage the coding and analysis process.

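### Randomly trimming clusters to an equal size discards outcome data the planned analysis could use and ties the result to an arbitrary draw

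*Protocol article*

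**What the plan says.** Four parts of the protocol article bear on this.

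- **Data analysis, first paragraph.** The reason given for trimming is: "Since the number of subjects/household members on whom data will be collected is expected to vary across clusters". The remedy is that the Stata sample "command will be used to randomly select an equal number of subjects across clusters for analysis". The paragraph closes with "All analyses will be on an intention-to-treat basis".
- **Data analysis, second paragraph.** The intervention effects are "computed from the unweighted mean of cluster-level summaries (proportions) of the outcome measures in each study arm". From the constant cluster size the authors conclude that "this point estimate will be identical to that obtained from the weighted average of individual values". Testing is by a stratified t test, using the residual mean square from a two-way ANOVA of cluster proportions.
- **Sample size.** A fixed 50 subjects of each target population "per cluster will be used to optimize statistical efficiency".
- **Sampling technique (recruitment).** On coverage, in the text after Fig. 3: "All the households in the selected clusters will be enumerated and screened for inclusion during the pre-intervention and post-intervention surveys". On reproducibility, for the selection of the 18 clusters only: "To enhance reproducibility, random-number seed will be set using the" usual Stata command.

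The article does not state how many subjects per cluster the analysis keeps. It describes no analysis of the full collected data.

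**The concern.** This is a positive rule about who enters the analysis, so it cannot be put down to condensation of a longer protocol. Every household is screened, numbers are expected to differ, and the surplus is then dropped.

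The estimator and the test both work on one proportion per cluster, and neither requires the denominators to be equal. Trimming a larger cluster raises the sampling variance of its proportion and lowers it in no other cluster. The efficiency argument for equal sizes applies when a fixed total is shared out among clusters. Here the total itself is reduced.

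Two things are at stake. One is precision, in a trial with only 6 clusters per arm. The other is arbitrariness: two equally legitimate draws from the same data can give different risk differences and fall on different sides of p = 0.05. The trial is open-label and the draw is made from data already collected, so such dependence is better avoided.

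The rule is stated for the household survey in general. It therefore reaches both co-primary outcomes and, if applied at baseline, adds noise to the baseline cluster summaries used as covariates in the adjusted analysis.

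**Working it through.** **Inputs from Sample size:** 31% versus 51% (the comparison that sets the sample size), 11% versus 31%, coefficient of variation k = 0.16, m = 40 per cluster raised to 50, 6 clusters per arm, 80% power, 5% type I error (two-sided assumed). **Assumptions:** 50 kept per cluster, because that is the target named under Sample size, and M collected per cluster, shown as a range because no figure is given.

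**1. The plan's own figure.** The number of clusters per arm is

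c = 1 + (1.96 + 0.84)² × [p0(1−p0)/m + p1(1−p1)/m + k²(p0² + p1²)] / (p0 − p1)².

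For 31% versus 51% and m = 40:
- p0(1−p0) + p1(1−p1) = 0.2139 + 0.2499 = 0.4638, and 0.4638/40 = 0.011595
- k²(p0² + p1²) = 0.0256 × 0.3562 = 0.009119
- sum = 0.020714
- c = 1 + 7.849 × 0.020714/0.04 = 5.06, rounded up to 6

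This agrees with the article. For 11% versus 31% the same formula gives 3.07.

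**2. Precision with and without trimming.** Var(difference) = [0.4638/m + 0.009119]/6.
- m = 50: (0.009276 + 0.009119)/6 = 0.003066, SE 5.54 points
- m = 75: (0.006184 + 0.009119)/6 = 0.002550, SE 5.05 points
- m = 100: (0.004638 + 0.009119)/6 = 0.002293, SE 4.79 points

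**3. Noise from the draw alone.** If 50 of M are drawn in each cluster, SD = √{(1/50 − 1/M) × 0.4638/6}. For M = 75 this is √(0.006667 × 0.0773) = 2.27 points.

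For 31% versus 51%:

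| Collected (M) | SE, all data (points) | SE, 50 kept (points) | Variance inflation | SD of the draw (points) |
|---|---|---|---|---|
| 50 | 5.54 | 5.54 | 0% | 0 |
| 55 | 5.41 | 5.54 | 5% | 1.2 |
| 60 | 5.30 | 5.54 | 9% | 1.6 |
| 75 | 5.05 | 5.54 | 20% | 2.3 |
| 100 | 4.79 | 5.54 | 34% | 2.8 |

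For 11% versus 31% the inflation is 7%, 13%, 30% and 53% at M = 55, 60, 75 and 100. If the number kept were 40 out of 50 collected, the inflation for 31% versus 51% would be 13% (SE 5.88 against 5.54).

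**4. Power.** For 31% versus 51% on the 9 residual degrees of freedom of the planned ANOVA (18 clusters in 9 stratum-by-arm cells), power is 89.4% with 50 per cluster. With all data it is 91.8% (M = 60), 94.0% (M = 75) or 95.9% (M = 100).

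**5. How often the draw changes the verdict.** The three-arm, three-stratum design was simulated 1,500 times per scenario, with 50 to 75 subjects collected per cluster, 50 kept, and 20 draws per simulated trial:

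| True difference (from 31%) | Power, all data | Power, trimmed | Trials in which the 20 draws disagree on p < 0.05 |
|---|---|---|---|
| 20 points | 95.7% | 93.9% | 15% |
| 15 points | 82.8% | 79.0% | 36% |
| 10 points | 57.2% | 52.0% | 50% |

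Across 20 draws the estimated difference ranged over about 6 points on average. Simulated power exceeds that in step 4 because the pooled residual includes the 11% arm, whose clusters vary less.

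**The case against.** **The surplus may be small.** The article names a target of 50 and plans for shortfall by revisiting households that were not eligible. That is consistent with clusters ending close to 50, and the loss is then near zero. This stands. A surplus of 75 to 100 is an assumption, since no fever prevalence is given, and figures for people aged 5 and above would need rates and a coefficient of variation that the article does not supply.

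**Power remains adequate.** With 50 kept, power at the planning values is 89.4%, above the 80% target. This also stands. The case rests on avoidable waste and arbitrariness and does not depend on inadequate power.

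**Equal sizes have some benefit.** They remove differences in sampling variance due to denominators, and they make the weighted and unweighted estimates coincide. The gain is slight. With v(p) = p(1−p)/m + k²p² and p = 31%, a cluster of 50 has variance 0.00674 and one of 75 has 0.00531, a ratio of 1.27. At the plan's own rates and 50 per cluster, the 51% and 11% arms have 0.01166 and 0.00227, a ratio of 5.1, which trimming leaves untouched.

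**A seed could be fixed.** The article sets one for cluster selection, and the seed for the subject draw may properly be left to an analysis plan. A seed makes the draw repeatable. The result still depends on it, and the precision is still lost.

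**Stronger readings a reader might infer.**
- *Breach of intention-to-treat.* Clusters are the randomised units, and all 18 stay in their allocated arm, so the principle is kept.
- *Bias or an invalid test.* A simple random subsample leaves each cluster proportion unbiased, and the observed between-cluster variance already contains the added noise.
- *The smallest cluster fixes the size for all 18.* This is one literal reading of the rule, but the article states no such thing and elsewhere names 50.

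**Conclusion.** The point holds as one of efficiency and arbitrariness. The article commits to leaving out collected outcome data for a cluster-level analysis that has no need of equal sizes, and the primary risk difference and p-value then depend on which subjects are drawn.

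At 31% versus 51%, k = 0.16, 6 clusters per arm and 50 kept, the cost runs from nothing (50 collected) through 5% and 9% extra variance (55 and 60) to 20% and 34% (75 and 100). The number collected is not in the document, so only this range can be given. Between-cluster variation, which trimming does not affect, limits the loss.

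The change should be made because it costs almost nothing. The flaw does not invalidate the trial.

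**What to change.** Before the end-of-study data are analysed:

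1. Delete the random selection of an equal number of subjects per cluster.
2. State that each cluster proportion is computed from all eligible consenting subjects surveyed in that cluster, at baseline and at end of study, for both co-primary outcomes.
3. Keep the unweighted stratified cluster-level t test.
4. Delete the sentence that weighted and unweighted estimates coincide because cluster size is constant. The following statement about strata rests on the number of clusters and can stay.
5. If wanted, report a size-weighted estimate, or an equal-size subsample with its seed fixed in advance, as a sensitivity analysis only.

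The cost is wording. Fieldwork, sample size and randomisation are unchanged. Cluster proportions will have somewhat unequal sampling variances, and the weighted and unweighted estimates will no longer be identical.

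### The optional log transformation conflicts with the planned risk difference and, if used with the three-arm residual variance, cuts power for the 31% v 51% comparison to about 55-64%

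*Protocol article*

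**What the plan says.** Protocol article, Data analysis. Intervention effects are risk differences, computed from the unweighted mean of the cluster proportions in each arm. An overall two-way analysis of variance on stratum and arm comes first. Next comes the option: "If the distribution of the cluster summaries in each study arm is markedly skewed, logarithmic transformation may be considered before analysis". The article then takes one residual mean square from the analysis of variance with interaction, fitted to all three arms, and uses it for every pair-wise stratified t test. Of the same variance it says: "It will also be used in computing the corresponding 95% confidence interval of each risk difference".

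Protocol article, Sample size. The size is set on absolute differences. Of the objective that drives it: "This is based on the primary objective to evaluate the effectiveness of the social group/provider intervention compared to the social group intervention". The inputs are "80% power at 5% probability of type I error", a rise from 31% to 51%, "Assuming a coefficient of variation between clusters within strata of 0.16" and "a sample size per cluster of 40 eligible children under 5 years of age", from which "the trial will require 6 clusters per arm". The cluster size is then raised: "This gives a final cluster size of 50 subjects with 300 subjects per arm". Control is assumed at 11%. Under Randomization, each of the three strata gives two clusters to each arm.

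**The concern.** The article names one effect measure and one interval, then allows a step that would change both. After a log transformation the t test compares geometric means, and its interval is for their ratio. The risk-difference interval promised shortly afterwards is not available from that analysis, and no log exists for a cluster in which no one was tested.

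The choice would rest on the shape of six values per arm, where sample skewness is a poor guide. The log is also not neutral here. On the natural scale the variance rises with the proportion; on the log scale it is largest in the 11% control arm. The planned pair-wise test pools all three arms, so control-arm noise would enter the 31% v 51% comparison, which is the one that sized the trial. At stake are the scale of the primary result and the power of that comparison.

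**Working it through.** **Inputs** (Sample size and Randomization): proportions 0.11, 0.31 and 0.51; between-cluster coefficient of variation k = 0.16; m = 40 or 50 per cluster; 6 clusters per arm, 2 per arm in each of 3 strata; 5% type I error, taken as two-sided to match the 95% interval.

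**1. The plan's own figure.** c = 1 + (1.96 + 0.84)² × [p₀(1−p₀)/m + p₁(1−p₁)/m + k²(p₀² + p₁²)] / (p₁ − p₀)².
For 31% v 51% at m = 40 the bracket is 0.00535 + 0.00625 + 0.00912 = 0.02071. So c = 1 + 7.85 × 0.02071/0.04 = 5.06, rounded up to 6. The stated figure is reproduced. For 11% v 31% the formula gives 3.07, so 31% v 51% does drive the size.

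**2. Variance of a cluster summary.** Natural scale: p(1−p)/m + k²p². Log scale, approximately: k² + (1−p)/(mp).

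| | 11% | 31% | 51% |
|---|---|---|---|
| Natural, m = 40 | 0.0028 | 0.0078 | 0.0129 |
| Log, m = 40 | 0.228 | 0.081 | 0.050 |
| Natural, m = 50 | 0.0023 | 0.0067 | 0.0117 |
| Log, m = 50 | 0.187 | 0.070 | 0.045 |

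**3. Power for 31% v 51% on logs, three-arm residual** (18 − 9 = 9 df). At m = 40 the pooled variance is (0.228 + 0.081 + 0.050)/3 = 0.120. The effect is ln(0.51/0.31) = 0.498 and its standard error √(2 × 0.120/6) = 0.200, so the non-centrality is 2.49 and power 0.60. At m = 50 the same steps give 0.68. Simulation of 60,000 trials, with zero counts replaced by 0.5, gives:

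| Variance taken from | Scale | m = 40 | m = 50 |
|---|---|---|---|
| Three arms, 9 df | natural | 0.91 | 0.94 |
| Three arms, 9 df | log | 0.55 | 0.64 |
| Two arms compared, 6 df | natural | 0.81 | 0.85 |
| Two arms compared, 6 df | log | 0.78-0.79 | 0.83 |

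With a two-arm variance the choice of scale costs only about 2 points. Pooling causes the loss.

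**4. The same pooling on the natural scale.** At m = 40 the pooled variance is (0.0028 + 0.0078 + 0.0129)/3 = 0.0078. The two arms compared average (0.0078 + 0.0129)/2 = 0.0104. The interval for 31% v 51% is therefore too narrow and misses the true difference in about 9% of simulated trials at either m, against about 5% with a two-arm variance. Part of the 0.91-0.94 is thus not real power. With control at 11% and both intervention arms at 31%, the pooled test of the two intervention arms rejects in 8.0% of trials on the natural scale and 2.0% on logs (m = 40).

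**5. Zero clusters.** With no between-cluster variation, 1 − (1 − 0.89⁴⁰)⁶ = 5.5%. With k = 0.16, simulation gives at least one zero cluster in about 7% of trials at m = 40 and 3% at m = 50.

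**6. How often chance triggers the switch.** The article gives no cut-off, so these are assumptions. The rule is that any arm has sample skewness above the cut-off:

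| Cut-off | Trials triggered | Average power, m = 40 | Average power, m = 50 |
|---|---|---|---|
| 1 | 35% | 0.79 | 0.84 |
| 1.5 | 15% | 0.86-0.87 | 0.90 |
| 2 | 3% | 0.90 | 0.93 |

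These averages use the three-arm residual and share the inflation shown in step 4. If all three arms must exceed 1, chance does this in 0.2-0.3% of trials for right skew and about 1% for skew in either direction.

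**7. Type I error.** Taking whichever scale is significant raises it from about 5% to 5.9-6.3% when all arms are equal.

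**The case against.** A reader might infer that noise will usually trigger the switch. The text does not support that. It speaks of skewness in each arm, which ordinarily means every arm, and then a chance trigger is about 1% or less. Counting skew in either direction in any arm gives about 54% at a cut-off of 1. That figure includes left skew, which a log would worsen, and the cut-off is not the plan's.

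A reader might also infer that the trial as planned falls below 80% power. Averaged over a right-skew rule it stays at about 79-93%, and the option is worded as a possibility only.

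Third, the sentence stands beside the overall test. The residual is still described in terms of proportions and the interval as one for a risk difference, so logs may never have been meant for the pair-wise tests. This is a fair reading, but the option applies before analysis without limit, so the text does not secure it.

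Fourth, a cut-off, a back-transformation and a rule for zero clusters could stand in an analysis plan not shown here. I do not count their absence. Nor does the article say who judges skewness or when, so deliberate choice after seeing results is not shown, and its cost would be small (step 7).

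The objection that carries most weight is that logs alone are not the culprit. Pooling across unequal variances is, and deleting the log option would leave that in place. This stands, and the fix covers it.

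**Conclusion.** The point holds in conditional form. The article lets observed skewness decide the scale of the primary test while promising risk-difference intervals that the log scale cannot give. If the option is used with the planned three-arm residual, power for the sizing comparison is about 55% (m = 40) or 64% (m = 50) instead of 80%, and 3-7% of trials would have a cluster without a log. Control v social group is not harmed (0.99 on logs against 0.96 at m = 40).

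The figures rest on the plan's own 11%, 31% and 51%, k = 0.16, a two-sided test, and 0.5 in place of zero counts. They give the consequence of using the option and do not predict that it will be used. The same pooling is a fault without logs, through an interval for 31% v 51% with about 9% non-coverage.

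**What to change.** - Delete the log option for the primary and co-primary proportions, and state that the natural-scale risk difference is primary whatever the shape of the cluster summaries.
- Keep any log-scale ratio only as a prespecified sensitivity analysis with a stated rule for clusters with no tested subject.
- Take the variance for each pair-wise test and interval from the two arms compared: 2 arms × 3 strata × 1 = 6 df. For 31% v 51% this gives about 5% non-coverage and simulated power of about 81% (m = 40) or 85% (m = 50).
- Name a stratified permutation test of the risk difference as the robustness check. Each pair has 6³ = 216 allocations, so the smallest two-sided p is 2/216 = 0.009. Simulated power for 31% v 51% is about 79% (m = 40) or 84% (m = 50), so at m = 40 it sits just under the 80% target. It serves as a check and does not replace the t test.

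The cost is a few sentences in the analysis section and a short Stata routine. The two-arm variance has fewer degrees of freedom and lower nominal power than the pooled test (0.81 against 0.91 at m = 40), but part of the pooled figure comes from an interval that is too narrow. No change to the number of clusters follows from this point.
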